### Data Collection

For each patient, the following demographic information will be recorded: age, gender, diabetes history, hypertension status, hyperlipidemia status, smoking status, peripheral arterial disease status, history of prior surgeries, history of previous percutaneous coronary intervention (PCI), and clinical manifestations (including asymptomatic, stroke, and TIA). Key laboratory test results (including blood creatinine, hemoglobin, and blood low-density lipoprotein [LDL] levels) and carotid plaque properties (soft or hard) determined by carotid ultrasound are also collected. The following angiographic and CAS procedure information will be collected, which including (1) aortic arch tortuosity (2) degree and location of extracranial and intracranial arterial stenosis (3) ulcer plaque and fresh thrombus in the stenotic carotid lesion (4) side of CAS procedure (5) type of embolic protection device (7) type, diameter and length of the carotid stent (8) balloon size, length, inflation pressure, duration as well as numbers of pre- and post- dilatation (9) procedure duration (10) procedure-related adverse events (including intraoperative and postoperative hemodynamic instability (11) intraoperative neurological deterioration (12). Other procedures in the same session, such as vertebral artery stenting and intracranial aneurysm embolization, etc.

### Outcomes

The primary outcome for this study will be the cumulative incidence of new ischemic lesions on post-CAS cerebral DW-MRI, TIA or ischemic stroke within 30 days after CAS. For this analysis, stroke is defined as any neurological deficits that persist for over 24 h by a vascular cause, including cerebral infarction, intracerebral hemorrhage (ICH), and subarachnoid hemorrhage (SAH). TIA is defined as any neurological deficit (cerebral or ocular) that is newly evident and consistent with focal cerebral ischemia but that resolved within a 24 h period (including localized muscular weakness, language dysfunction, transient monocular blindness, or the need for assistance while walking.

In addition, this study will have the following secondary outcomes: (1) the incidence of new ischemic lesions as detected via cerebral DW-MRI within the period of 5-day following CAS; (2) the number of new lesions and the incidence of new lesions >5 mm in size as detected via DW-MRI within this 5-day postoperative period; (3) the incidence of ischemic stroke or TIA within 30 days postoperative period; (4) the incidence of death, any stroke, or myocardial infarction within 30 days postoperative period; (5) rates of bleeding complications, as determined based upon the Thrombolysis In Myocardial Infarction criteria (8), and of entry-site complications (subcutaneous hematoma >10 cm, pseudoaneurysm or arteriovenous fistula).

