### Intervention

Individuals in the high-dose group will be administered 80 mg/day atorvastatin beginning 3 days prior to CAS and continuing until 3 days following CAS, whereas routine treatment group patients will receive 20 mg/day atorvastatin during this same period. For the remainder of hospitalization and after discharge, all patients will be administered 20 mg/day atorvastatin. Cerebral protection devices will be required for all patients, but the form of the protective device, the type of stent used, and the interventional strategy will be left to clinical discretion.

Before the CAS procedure, six-vessel DSA is routinely performed. Symptomatic patients with carotid stenosis <50% and asymptomatic patients with carotid stenosis <70% confirmed by cerebral angiography will be excluded from this study.

During the CAS procedure, the distal embolic protection device will be used for all patients. Type of distal protective device (Spider FX., Medtronic; Emboshield NAV, Abbott), carotid stent (Precise, Cordis; Protégé, Medtronic; Acculink, Abbott), pre- and post- dilatation balloon (Ryujin plus, Terumo; Sterling, Boston Scientific, Viatrac, Abbott) will be left to operators' discretion.

Within 5 days prior to CAS, all patients will undergo an MRI examination (including DW-MRI), a neurological assessment, and blood sampling in order to test for parameters such as hematological findings, lipid levels, and hepatic/renal function. In addition, all patients will receive routine standard of care treatment including aspirin (100 mg/day prior to CAS for ≥ 3 days, or a 300 mg loading dose at 6 h prior to CAS) and clopidogrel (75 mg/ day prior to CAS for ≥ 3 days, or a 300 mg loading dose at 6 h prior to CAS). All patients will receive platelet aggregation tests using optical aggregometry before the procedure, and those who show clopidogrel resistance will switching to ticagrelor 90 mg, twice a day. Patients will then undergo routine conventional dual antiplatelet aggregation treatment for 3 months, followed by long-term aspirin administration (100 mg/day). Within 5 days following the CAS operation, all study subjects will again be subjected to DW-MRI and blood tests of the same parameters measured preoperatively.

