### MRI Protocol

MRI was performed using a 1.5T imaging unit (Optima MR360, G.E. Medical Systems). Sequences were applied at the same level, with the same slice thickness and same cut number. Slice thickness comprised the cut thickness (5 mm) plus gap (10 per cent). The standard number of slices was 20.

New ischemic lesions in the brain were defined as hyperintense lesions on postintervention diffusion-weighted imaging that were not present on pretreatment MRI. The pre- and post-operative DW-MRI findings will be compared. New ischemic lesions will be recorded based on the following criteria: whether any are present, their localization, their total number, their maximum diameter (with fully separated lesions on the same level or continuous levels being considered to be a single lesion; Ischemic foci localization will be recorded as “ipsilateral,” “contralateral,” or in “posterior circulation” relative to CAS). Two neuroradiologists with more than 10 years of experience, blinded to patient history and intervention procedure information, will independently analyze all MRI images and will discuss and agree upon these results when their judgements are inconsistent. If no consensus could be reached, a third reviewer had the final decision.

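### The 30-day clinical outcomes start at CAS although the arms differ from 3 days before it, so strokes, TIAs, infarctions and deaths on randomised drug before the procedure are left out

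*Protocol article*

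**What the plan says.** **Dosing.** In the Protocol article, section Intervention, the high-dose arm receives "80 mg/day atorvastatin beginning 3 days prior to CAS and continuing until 3 days following CAS". The comparator is given over the same days and is worded as follows: "whereas routine treatment group patients will receive 20 mg/day atorvastatin during this same period". The Intervention row of the Appendix table gives the same dates. The randomised contrast therefore begins on day -3.

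**Outcomes.** In the Outcomes section, the primary outcome is the cumulative incidence of "new ischemic lesions on post-CAS cerebral DW-MRI, TIA or ischemic stroke within 30 days after CAS". Secondary outcome 3 is "the incidence of ischemic stroke or TIA within 30 days postoperative period" and secondary outcome 4 is "the incidence of death, any stroke, or myocardial infarction within 30 days postoperative period". Secondary outcome 5 covers "rates of bleeding complications, as determined based upon the Thrombolysis In Myocardial Infarction criteria", together with entry-site complications, and states neither a start nor an end.

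**Imaging.** Baseline imaging is scheduled as follows: "Within 5 days prior to CAS, all patients will undergo an MRI examination (including DW-MRI), a neurological assessment, and blood sampling". The MRI Protocol section defines new lesions as "hyperintense lesions on postintervention diffusion-weighted imaging that were not present on pretreatment MRI".

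**Aim.** The Introduction gives a secondary aim: to find out whether the normal-dose and high-dose regimens differ in safety.

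**The concern.** A safety comparison of two regimens should cover the time for which patients take them. Here the regimens already differ for 3 days before the clock for the clinical outcomes starts. Take a patient who has an infarction, a hemorrhagic stroke or a TIA on day -2, on randomised drug. As the outcomes are worded, that event meets neither secondary outcome 3 nor 4, nor the clinical part of the primary outcome.

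The case that matters most is an event that leads to cancellation of CAS. That patient has no postoperative period and no post-CAS scan, and so cannot contribute to any outcome anchored on CAS. With 65 patients planned per arm, deaths, strokes and infarctions may be few, and one or two uncounted events could change how the safety table reads.

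This is not detail that a condensed article leaves to a fuller document. The article does fix the windows of secondary outcomes 3 and 4, and those windows do not match the exposure that the safety aim concerns.

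**Working it through.** The plan gives no figure for pre-CAS events, so there is none to reproduce. The sample size calculation does not depend on this point; only its total of 130 (65 per arm) is used below.

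**Step 1. Dosing and outcome windows side by side**

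| Item | Start | End | Event between first dose and CAS |
|---|---|---|---|
| Arm-different dosing | day -3 | day +3 | not applicable |
| Primary, TIA or ischemic stroke | CAS | day 30 | not counted |
| Primary and secondary 1 and 2, DW-MRI lesion | baseline MRI, within 5 days before CAS | post-CAS scan, within 5 days after CAS | counted if the lesion arises after the baseline MRI and the scan is done |
| Secondary 3, ischemic stroke or TIA | CAS | day 30 | not counted |
| Secondary 4, death, any stroke or infarction | CAS | day 30 | not counted |
| Secondary 5, bleeding and entry site | not stated | not stated | undefined |

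The imaging row follows from the definition of a new lesion. The comparison is between two scans, so it covers whatever happens between them, including part or all of the pre-CAS dosing. It does not capture death, infarction, hemorrhagic stroke as a clinical event, a TIA without a DW-MRI lesion, or any event that prevents CAS or the scan.

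**Step 2. Share of arm-different dosing before CAS**

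- Counting the day of CAS: days -3 to +3 are 7 days, and 3/7 = 43%.
- Not counting it: 3/6 = 50%.

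This is a share of dosing days. It is not a share of risk or of events, since the plan expects risk to concentrate around the procedure.

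**Step 3. Possible number of uncounted events**

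The 3-day risk *r* of a clinical stroke, TIA, infarction or death before CAS is an assumption. Expected events = 130 × *r*. Chance of at least one = 1 − (1 − *r*)^130.

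| Assumed *r* | Expected in 130 | Chance of at least one |
|---|---|---|
| 0.1% | 0.13 | 12% |
| 0.5% | 0.65 | 48% |
| 1% | 1.3 | 73% |
| 2% | 2.6 | 93% |

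Per arm of 65, the expected number runs from 0.065 to 1.3.

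**Step 4. How plausible the upper rows are**

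At a constant hazard, a 3-day risk *r* corresponds to a yearly risk of 1 − (1 − *r*)^(365/3). This gives about 11% for *r* = 0.1%, 46% for 0.5% and 91% for 2%. The rows from 0.5% upward therefore describe a very high background rate, and the lower end of the range deserves more weight unless the sponsor has data to the contrary.

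**The case against.** **The procedure is the natural origin.** The trial asks about periprocedural ischemic injury, and counting from CAS fits that question. This stands for the primary outcome, which should keep its window. It is weaker for the safety aim, which concerns the regimens, and those include the days before CAS.

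**Few patients are affected.** A patient with a TIA on day -2 who still has CAS stays in the comparison and can contribute later events. Only a patient who never reaches CAS is lost altogether, and how such patients are analysed may be set out in the statistical analysis plan. This stands in part: the pre-CAS event itself is still uncounted under the windows as printed, and an analysis set does not change that.

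**Stronger readings that the documents do not support.**

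- A reader might infer that events in the pre-CAS phase count nowhere. They do not all vanish: a lesion arising after the baseline MRI is new on the post-CAS scan and counts in the primary outcome and in secondary outcomes 1 and 2, provided CAS and the scan take place. The post-CAS blood tests, which include hepatic and renal function, can also show laboratory effects of the early doses, although they are not a listed outcome.
- A reader might infer that pre-CAS bleeding is excluded, or that bleeds weeks later are counted inconsistently. An outcome with no stated window excludes nothing. Every other clinical outcome ends at 30 days, and no later study visit is described. This is a missing detail that a fuller document may supply.
- A reader might infer that the safety comparison covers only patients who came through the pre-CAS dosing without an event. That does not follow, because patients with an event who still have CAS remain in it.

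**Conclusion.** The mismatch is real and follows directly from the text: the randomised contrast starts on day -3, while secondary outcomes 3 and 4 and the clinical part of the primary outcome start at CAS. Clinical stroke, TIA, infarction or death in between is omitted from those outcomes, including an event that cancels the procedure.

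The size is uncertain and probably small. It rests wholly on an assumed 3-day risk: 0.1% to 2% gives about 0.1 to 2.6 uncounted events in the whole trial, with the lower end more plausible. The primary comparison should hardly be affected, because the assumed 40% control rate draws on post-CAS DW-MRI lesions and the gap lasts 3 days. What is at stake is the completeness of the safety comparison. Severity: minor.

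**What to change.** In the Outcomes section, define secondary outcomes 3 and 4 as counted from the first randomised dose to 30 days after CAS, or to 30 days after the planned CAS date if CAS is cancelled, in all randomised patients who took at least one dose. Report the from-procedure count beside it, by arm. Leave the primary outcome periprocedural. While that text is open, print a start and an end for secondary outcome 5; this is a clarification only.

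The cost is a sentence or two of text and a few more days of event collection per patient, plus follow-up to the 30-day point for the few whose CAS is cancelled. The change alters no treatment, sample size or primary endpoint. The drawback is that the extended rates are slightly less comparable with studies that count from the procedure, and the second count deals with that.

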### Sample Size Estimates

The open-source Open-EPI v3.03 software was used for sample size calculations for the present study. The test level α is 0.05 (two-sided test), and the test efficiency Power (1-β) is 0.08. Based upon findings in the abovementioned meta-analysis and the ARMYDA-9 CAROTID study, we estimated a primary endpoint incidence of 40% in routine-dose control group patients. In contrast, the incidence in the high-dose treatment group, who will undergo therapy longer than did patients in the ARMYDA-9 CAROTID study, was estimated to be lower at 15%. Given a 1:1 control to test group ratio, it was estimated that the control group would require 56 test cases. Given a predicted 15% dropout rates, a required sample size of 65 was calculated for both groups, yielding an overall sample size of 130.

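### The stated power of 0.08 cannot produce the 56 patients per arm derived in the same paragraph; it is most likely a misprint for 0.80 and should be confirmed and corrected

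*Protocol article*

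**What the plan says.** Everything is in the Sample Size Estimates section of the protocol article. Alpha is 0.05, two-sided. On power, the text reads "the test efficiency Power (1-β) is 0.08". For the event rates, "we estimated a primary endpoint incidence of 40% in routine-dose control group patients", and 15% is assumed in the high-dose group. Allocation is 1:1. The result is that "it was estimated that the control group would require 56 test cases", which with equal allocation means 56 in each arm. The dropout step follows: "Given a predicted 15% dropout rates, a required sample size of 65 was calculated for both groups", for a total of 130.

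The section names the software but not the sample-size formula, whether a continuity correction was used, or the formula for the dropout allowance. The Statistical Analyses section allows either a chi-squared test or Fisher's exact test for categorical outcomes. No other section states the power.

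**The concern.** A power of 0.08 is an 8% chance of detecting the planned difference, and no trial is sized for that. The label (1-β) stands beside the figure, so it cannot be read as β or as alpha. Since no other section gives the power, nothing in the document corrects it.

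Power is one of the figures that a reader uses to judge a null result from a trial of 130 patients. A reader who takes the paragraph literally is misinformed, and one who recognises a misprint still has to guess the intended value. The dropout step also deserves a check, because 65 less 15% falls slightly below the 56 that the section says it needs.

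**Working it through.** **Inputs**, all from the Sample Size Estimates section: p1 = 0.40, p2 = 0.15, difference d = 0.25, alpha 0.05 two-sided (z = 1.960), 1:1 allocation, 15% dropout. The formula is not stated, so I assume the usual two-proportion formula with pooled variance under the null (Fleiss):

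n = [1.960·√(2·p̄·(1−p̄)) + z(power)·√(p1(1−p1) + p2(1−p2))]² / d²

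Here p̄ = (0.40 + 0.15)/2 = 0.275. The first root is √0.39875 = 0.6315 and the second is √(0.24 + 0.1275) = √0.3675 = 0.6062. The first term is therefore 1.960 × 0.6315 = 1.2377. The continuity-corrected size is n_c = (n/4)·[1 + √(1 + 4/(n·d))]².

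**Step 1. Can the plan's 56 be reproduced?**

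| Power | z(power) | n uncorrected | n with continuity correction |
|---|---|---|---|
| 0.08 (as printed) | −1.405 | (1.2377 − 0.8518)²/0.0625 = 2.4, so 3 | 8.5, so 9 |
| 0.80 | 0.842 | (1.2377 + 0.5102)²/0.0625 = 48.9, so 49 | 56.6, so 57 |
| 0.85 | 1.036 | (1.2377 + 0.6283)²/0.0625 = 55.7, so 56 | 63.5, so 64 |

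At the printed power, neither version comes near 56. At 0.80 the corrected formula comes within one patient of it. At 0.85 the uncorrected formula gives exactly 56.

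**Step 2. What power do the planned numbers give?** Exact power for 40% against 15%, by enumerating both binomial distributions:

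| Evaluable per arm | Chi-squared, uncorrected | Fisher's exact |
|---|---|---|
| 56 | 0.859 | 0.808 |
| 55 | 0.852 | 0.798 |

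So 56 per arm fits an intended 0.80 under Fisher's test, and about 0.85 under the uncorrected chi-squared test. The figures alone do not settle which was meant.

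**Step 3. The dropout allowance.** Retained from 65: 65 × 0.85 = 55.25, which is 0.75 of a patient below 56. To keep 56 one needs 56/0.85 = 65.9, so 66 per arm and 132 in total. The printed 65 agrees with 56 × 1.15 = 64.4 rounded up, and also with 65.9 cut down to a whole number. From the table in Step 2, going from 56 to 55 costs 0.859 − 0.852 = 0.007 under chi-squared and 0.808 − 0.798 = 0.010 under Fisher's test.

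**The case against.** The strongest reply is that 0.08 is plainly a slip for 0.80 and that nothing was built on it. The sizes of 56, 65 and 130 are all compatible with a power of 0.80 or somewhat more, under either test that the Statistical Analyses section allows. This largely stands. It settles that the sample size is sound, but it does not make the printed figure right. Nor does it fix the intended value beyond doubt, since 56 matches 0.85 exactly without a correction and matches 0.80 only to within one patient with one.

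It can also be said that an article may leave the formula to the full protocol. That is fair, and the unnamed formula is not counted as an error here. The power, however, is not left out; it is stated wrongly.

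On dropout, the 15% is itself a prediction, and a gap of less than one patient per arm is well within its uncertainty. That stands in full.

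Two stronger readings are tempting. A reader might infer that the trial was really planned with an 8% chance of success, or is underpowered for its target effect; the exact powers above contradict this. A reader might also infer that the dropout allowance was made by multiplying by 1.15 instead of dividing by 0.85. The document does not show this, because no formula is given and cutting 65.9 down to 65 gives the same number.

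**Conclusion.** The stated power is wrong as printed: 3 or 9 per arm would be enough for it, against the 56 derived beside it. The likeliest intended value is 0.80, with 0.85 as the alternative that the arithmetic leaves open. This should be fixed as a correction of a stated planning figure; it is not a design flaw, and it gives no reason to change the 130.

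The dropout shortfall is true but minor, at no more than about one point of power. It has no part in making the stated power wrong.

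These conclusions rest on the section's own event rates, on 15% loss in each arm, and on the standard two-proportion formula. The mismatch at 0.08 is far too large to depend on the choice of formula. The choice between 0.80 and 0.85 does depend on it.

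**What to change.** 1. The sponsor should confirm the intended power from the original calculation and correct the figure in the Sample Size Estimates section. A short note of whether that calculation was continuity-corrected, exact or uncorrected would remove the remaining ambiguity.
2. Keep 130 and restate what it delivers. Possible wording: 130 patients randomised, about 55 evaluable per arm after 15% dropout, giving power for 40% against 15% of about 0.85 with an uncorrected chi-squared test, or just under 0.80 with Fisher's exact test.
3. If 56 evaluable per arm is to be kept as a firm requirement, the matching enrolment is 66 per arm, 132 in total.

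Items 1 and 2 change wording only and add no patients. Item 3 is optional and would add two.

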### Statistical Analyses

All categorical variables will be given as percentages, while continuous variables will be means ± standard deviations. Chi-squared tests or Fisher's exact tests will be used to compare categorical variables, whereas continuous variables will be analyzed via *t*-tests or a *U*-tests.

These statistical methods will be used to compare whether there are any differences between the control and test groups at baseline, and whether there are any differences in perioperative ischemic brain injury incidence between these groups. *P* < 0.05 will be the significance threshold. In addition, univariate and multivariate logistic regression analyses will be used as a means of identifying any risk factors associated with the incidence of perioperative ischemic brain injury (primary endpoint and partial secondary endpoint) in CAS patients. Prespecified subgroup analysis will be conducted according to whether age is > 70 years and whether symptomatic or not.

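### The randomised arms are to be compared at baseline by P < 0.05 tests, which are uninformative, while the treatment comparison is unadjusted; a descriptive baseline table and one prespecified adjusted model would be modestly better

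*Protocol article*

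**What the plan says.** The Statistical Analyses section gives one set of two-group methods for all comparisons. For categorical variables: "Chi-squared tests or Fisher's exact tests will be used to compare categorical variables". The same methods serve two purposes. The first is to "compare whether there are any differences between the control and test groups at baseline". The second is the difference between arms in perioperative ischemic brain injury. One threshold covers both: "0.05 will be the significance threshold".

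The section then adds a regression: "univariate and multivariate logistic regression analyses will be used as a means of identifying any risk factors" for the primary endpoint and some secondary endpoints. It names no covariates and no adjusted treatment effect.

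Data Collection lists "age, gender, diabetes history, hypertension status, hyperlipidemia status, smoking status, peripheral arterial disease status, history of prior surgeries", then previous PCI, clinical presentation and three laboratory values. It also states that "carotid plaque properties (soft or hard) determined by carotid ultrasound are also collected". That makes 14 items before the angiographic ones. Under Randomization, allocation is stratified by age (above 70 or not) and by symptomatic status, so plaque type is not balanced by design.

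**The concern.** When arms are formed by randomisation, any baseline difference is due to chance. A significance test at baseline therefore tests a hypothesis already known to be true. A small P value says only that chance produced a visible difference. A large one does not show that an imbalance is harmless, because what matters is the size of the imbalance and how strongly the factor predicts the outcome.

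The stated treatment comparison is a two-group test that cannot use baseline information. It uses neither the two stratification factors nor plaque type, which is collected before the procedure and could plausibly bear on embolic risk. A model fixed in advance would use these values whatever the baseline P values turn out to be, and would leave no room to choose adjustments after seeing the baseline table.

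**Working it through.** **Inputs from the protocol article.** Sample Size Estimates: 40% vs 15%, two-sided α 0.05, 56 per arm, 65 per arm after 15% dropout. Data Collection: 14 baseline items, or 12 without the two stratification factors. Statistical Analyses: threshold 0.05.

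**Inputs assumed.** Prevalence of soft plaque (45% or 50%) and its odds ratio for the primary outcome (2 to 5). The documents give neither.

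**1. The plan's own figure.** With power read as 0.80 (the printed 0.08 would need only 3 per arm):
- n = [1.96·√(2·0.275·0.725) + 0.842·√(0.40·0.60 + 0.15·0.85)]² / 0.25² = 48.9, so 49.
- With continuity correction, 57, against 56 stated. The figure is reproduced within one patient per arm.

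**2. Chance of at least one baseline P < 0.05 under sound randomisation.** For k independent tests it is 1 − 0.95^k.
- k = 12: 1 − 0.95¹² = 46.0%.
- k = 14: 1 − 0.95¹⁴ = 51.2%.
- Simulation at 65 per arm with correlated variables (latent correlation 0.3): 43% for 12 items and 49% for 14.

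**3. Imbalance that the tests let pass.** z = d / √(2·p̄(1 − p̄)/n), not significant while z < 1.96.

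| Reference arm (n = 65) | Largest unflagged | Smallest flagged |
|---|---|---|
| 20% | 13.8 points | 15.4 points |
| 31% | 15.4 points | 16.9 points |
| 40% | 16.9 points | 18.5 points |

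At 56 per arm the largest unflagged imbalance is 16 to 18 points. The tests would flag a 50% vs 65% difference with a probability of only 41% at 65 per arm and 36% at 56.

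**4. What an unflagged imbalance could do (assumed prognostic strength).** With 45% prevalence, odds ratio 3 and a control rate of 40%, the risks are 54% (soft) and 28% (hard). A 15-point imbalance shifts one arm's rate by 0.15 × (0.54 − 0.28) = 0.039, about 4 points. Adding 4 points to the high-dose rate, with 65 per arm:

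| Events, routine vs high dose | P as observed | P after shift |
|---|---|---|
| 26 vs 10 (the planned effect) | 0.002 | 0.010 |
| 26 vs 13 | 0.013 | 0.051 |
| 26 vs 15 | 0.038 | 0.12 |

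**5. Power, unadjusted test vs logistic model with the factor** (simulated, 56 per arm, 40% vs 15%, prevalence 45%).

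| Assumed odds ratio | Unadjusted | Adjusted |
|---|---|---|
| 2 | 87% | 87% |
| 3 | 86% | 88% |
| 5 | 86% | 90% |

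Type I error was about 5.0-5.5% for both tests. About 25% of simulated trials had an unflagged imbalance of 10 points or more. Within those, power was 84% vs 88% (odds ratio 3) and 83% vs 89% (odds ratio 5).

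**6. Events available for a model.** (0.40 + 0.15) × 56 = 30.8 and (0.40 + 0.15) × 65 = 35.75, so about 31 to 36. Four terms leave about 30.8/4 = 7.7 to 35.75/4 = 8.9 events per term.

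**The case against.** The strongest reply is that nothing in the stated analysis depends on the baseline tests. The article says that differences will be looked for, not what follows from finding one. A reader might infer that comparability is decided by P < 0.05 and that the primary result is thereby distorted. The text does not support this: the outcome test runs the same way whatever the baseline table shows. Its error rate already allows for chance imbalance. This part of the reply stands, and deleting the baseline tests would by itself change no result.

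A reader might also infer that prognostic factors are adjusted for nowhere. That goes too far as well. A multivariate logistic regression on the primary endpoint is planned, and treatment and plaque type could both enter it. But its stated purpose is to find risk factors, and it is not declared as an estimate of the treatment effect.

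A third reply is that covariate lists commonly sit in a statistical analysis plan, which is not shown. So the missing list is not counted as an error. The point rests on what the article does state: significance tests at baseline, and a two-group test for the treatment comparison.

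Finally, no passage says how common soft plaque is or how strongly it predicts new lesions. That stands, and it limits any claim about size. The false-alarm figure is also conditional, because the article does not say which items will be tested.

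**Conclusion.** The point holds as a modest improvement. The baseline tests are uninformative: about 43-51% of sound trials would show at least one P < 0.05 if 12 to 14 items are tested. Binary factors are flagged only from about 15 to 18 points at 65 per arm. The primary test remains valid.

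A prespecified adjusted estimate is a better method than the unadjusted comparison stated. It gains about 0 to 4 points of power for assumed odds ratios of 2 to 5, starting from 86-87%, and nothing visible at an odds ratio of 2. It would be tempting to say that unflagged imbalance could overturn the trial's result. At the planned effect it does not: under the assumed 4-point shift P stays at 0.010. Only results nearer the threshold cross it, so the protection matters mainly if the true effect is smaller than the planned 25 points.

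**What to change.** - Remove the baseline significance tests. Show baseline values by arm descriptively, with standardised differences if wanted.
- State that the treatment effect on the primary outcome is estimated in a logistic model with treatment, age > 70, symptomatic status and plaque type (soft or hard). All terms stay in whatever the baseline table shows. Report an adjusted odds ratio or risk difference with 95% CI.
- Keep this model separate from the risk-factor regression, and limit it to these 3-4 terms.

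The cost is a change of wording and one model. Sample size, procedures and data collection stay as they are. The downside is some model dependence with about 31-36 events, which is why the list should be short and fixed in advance.
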